During Imaging, if the removal of a fluorescent lesion does not change the magnitude of the operation, then it can be removed. Until we have more data on the false positive rate of our technology, we will not change the magnitude of the operation based on results from an investigational drug. Lesions that are identified by the surgeon and not the imaging system will be removed at the surgeons' discretion following the standard of care operation.

The duration of surgical procedures to resect thoracic malignancies varies substantially, anywhere from 2- 6 hours or more. It is estimated that visualization of the chest and removal of nodules for the purposes of this study will require an additional ten (10) minutes. Due to potential quenching of the fluorophore, visualization time will be limited to 30 minutes.

The visualization will be conducted with a camera: The Artemis Handheld Camera System-- open-field and laparoscopic-- manufactured by the Quest Medical Imaging. The Artemis has received approval from the FDA for a Phase II ovarian cancer clinical trial in Ohio, The Artemis is registered with the FDA for fluorescence imaging. The Artemis systems are proposed to be non-significant risk (NSR) devices as the devices do not meet the criteria of a significant risk device defined in 21CFR 812.3 (m). Another camera that will be used for visualization is called the Spectropath FLI-10A which is manufactured by Nanjing NuoYuan Medical. The cameras will be stored in the offices in operating room that stores the camera towers and will be used for the surgeries. The camera will be rolled into the operating room by the surgeon performing the case.

There is a chance that being under anesthesia for the additional five (5) to ten (10) minutes could put the subject at an increased risk of having a common side effect associated with anesthesia. These common side effects include, but are not limited to: nausea and vomiting after surgery, sore throat and hoarseness, shivering/chills, confusion, and muscle aches.

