### 3.2 Study Endpoints

#### Efficacy

Efficacy will be assessed through determination of the sensitivity and specificity of SGM-101 uptake and expression in identifying non-small cell lung cancer. Additional exploratory efficacy outcomes will include:

- Number of lung nodules lesions identified under usual visual/tactile conditions compared with such lesions identified using SGM-101 and fluorescence imaging
- Number of lymph nodes with metastatic cancer that are identified using visual/tactile conditions compared with such lesions identified using SGM-101 and fluorescence imaging
- Proportion of subjects in whom more lesions are identified using SGM-101 with fluorescence imaging and subsequently confirmed by pathology/immunohistochemistry analysis as cancer compared with using usual visual/tactile conditions to identify such lesions
- Number of cases that surgeon cuts through tumor and the positive margin is detected by the imaging of SGM-101.

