## 6.3 Visit 3- Surgery

During the operation, imaging will take place before resection and after resection. Before resection, the surgeon will perform the standard of care operation in order to expose the tumor. Once the lung is exposed, the surgeon will use the intraoperative imaging device to videotape and discover if the tumor is fluorescent. Also, the surgeons will determine if there are any additional lesions that are fluorescent.

Once this is accomplished, we will proceed with the standard-of-care operation and resection. Then once the tumor is removed, the camera will be re-inserted to determine if there are any additional lesions still in the chest. If there is a lesion left behind, the surgeon will determine if this can be biopsied or not. If removing the additional lesion

would significantly alter the magnitude of the operation, then the nodule or residual cancer will not be removed. It can be monitored postoperatively by CAT scans. In this study, until we are confident of the false positive rate, no additional surgery will be performed based on imaging results alone. If the surgeon using his experience feels this additional location is cancer, then it will be biopsied and/or removed.

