The sensitivity will be based on the single lung nodule that is being removed in a patient. Typically for lung cancer surgery, we are there to remove one nodule. That will be the basis of the calculations. Thus, the denominator will be 10 patients for the first Cohort, and another 10 patients for the second Cohort. (A total of 20 data points for the whole study). The calculations will be based on two pieces of data: tumor fluorescence and pathology. We will not be doing a detailed IHC study at this time.

If successful, we will consider 10 more subjects. Then, with 20 subjects, we will have 90% power to identify any unforeseen adverse event that occurs with a prevalence of at least 5%. We will use a Bayesian continuous safety monitoring design that registers a signal if the posterior probability that the chance of an adverse reaction is greater than 0.1 exceeds 80%. If we encounter a safety signal, we will suspend enrollment until the issue has been addressed.

The fraction of tumors on pathology that are identified by the imaging procedure will provide an estimate of the sensitivity of the procedure. Of the 20 enrolled subjects, we expect approximately 60%, or 12, to have fluorescent tumors. With 12 tumors, an exact 95% confidence interval for sensitivity would range from (0%, 12%) if no tumors are detected up to (88%, 100%) if all 12 are detected. We will compute estimates of the sensitivity (fraction of path-positive margins that are called correctly) and specificity (fraction of path-negative margins that are called correctly), and calculate 95% confidence intervals around them. A second aim will be to estimate the sensitivity of the procedure for identifying all lesions, including lesions that were not pre-identified. Because some subjects will contribute more than one lesion, we will estimate these parameters using random effects logistic regression models (in SAS Proc Glimmix) that allow for between-subject variability. These specimens will provide independent estimates of the positive and negative predictive values of discovering satellite nodules.

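### Sections 3.1 and 6.3 disagree on whether a minor lesion seen only by fluorescence may be removed, so which added lesions reach pathology depends on the section followed

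*Protocol*

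**What the plan says.** Section 3.1 (General Design) says that "if the removal of a fluorescent lesion does not change the magnitude of the operation, then it can be removed". The limit it sets is on scale: until more is known about false positives, "we will not change the magnitude of the operation based on results from an investigational drug". It does not require the surgeon to suspect the lesion independently.

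Section 6.3 (Visit 3, Surgery) gives four instructions on lesions found after resection:

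- On biopsy: "If there is a lesion left behind, the surgeon will determine if this can be biopsied or not".
- On scale: if removing the added lesion "would significantly alter the magnitude of the operation, then the nodule or residual cancer will not be removed".
- On imaging as the only reason: "until we are confident of the false positive rate, no additional surgery will be performed based on imaging results alone".
- On the surgeon's judgement: "If the surgeon using his experience feels this additional location is cancer, then it will be biopsied and/or removed".

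Two parts of the analysis need pathology on added lesions. Section 3.2 lists as an exploratory outcome the "Proportion of subjects in whom more lesions are identified using SGM-101 with fluorescence imaging and subsequently confirmed by pathology/immunohistochemistry analysis as cancer", compared with usual visual and tactile identification. Section 7.1 states: "A second aim will be to estimate the sensitivity of the procedure for identifying all lesions, including lesions that were not pre-identified". It then promises positive and negative predictive values for satellite nodules. The main sensitivity estimate in section 7.1 uses only the one planned nodule per patient.

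**The concern.** Consider an added lesion that fluoresces, that the surgeon would not otherwise suspect, and that could be taken without enlarging the operation. Section 3.1 permits its removal. The general bar in section 6.3 does not. Two surgeons, or one surgeon on two days, could act differently on such a lesion and each cite the protocol.

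The statistical stake is selective verification. If section 6.3 governs, an added fluorescent lesion tends to reach pathology only when the surgeon also suspects it. The lesions that then supply the predictive values and the all-lesion sensitivity are filtered by the very judgement with which fluorescence is being compared. If section 3.1 governs, the filter is weaker. A mixture of the two practices gives an estimate that belongs to neither rule.

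**Working it through.** The protocol states no figure on this point, so there is none to reproduce. The check has three parts.

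**1. The rules side by side**

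| Added fluorescent lesion | Section 3.1 | Section 6.3 |
|---|---|---|
| Removal would change the scale of the operation | Not on the strength of the drug's results | Not removed |
| Minor removal, surgeon also suspects cancer | Permitted | Biopsied and/or removed |
| Minor removal, seen only by imaging | Permitted | Removal barred for now; an earlier sentence leaves biopsy to the surgeon |

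The sections conflict only in the last row. The bar in section 6.3 is temporary, but no criterion says when it lifts.

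**2. Direction of the effect**

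Let there be *m* malignant and *b* benign added fluorescent lesions. Let a share *s1* of the malignant and *s0* of the benign ones reach pathology. The predictive value among verified lesions is

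PPV = m·s1 / (m·s1 + b·s0).

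This equals the full-sample value m/(m + b) when s1 = s0 and exceeds it when s1 > s0, that is, when the surgeon's suspicion carries information. For all-lesion sensitivity, TP/(TP + FN), leaving *k* fluorescence-only cancers unsampled gives (TP − k)/(TP − k + FN). With FN above zero this is lower. FN is the same under either rule, because section 3.1 leaves lesions that the surgeon sees and imaging misses to standard care. So a strict section 6.3 would tend to raise the predictive value and lower the all-lesion sensitivity relative to section 3.1.

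**3. Possible size for the section 3.2 outcome (illustration only)**

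Inputs:

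- n = 20 subjects (section 7.2).
- q = share of subjects with an added cancer shown by fluorescence and removable without changing the scale of surgery. **This is an assumption.** The only figure at hand is from the earlier colorectal patients in section 1.4: 8 of 61 had additional lesions, 8/61 = 13.1%. A range of 5% to 20% is shown around it.
- s = share of those subjects in whom the rule in force lets the lesion reach pathology. s = 1 is section 3.1 with the permission always used. s = 0 is a strict section 6.3 with no independent suspicion and no discretionary biopsy. s = 0.5 lies between.

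Expected subjects = 20·q·s. P(at least one) = 1 − (1 − q·s)^20.

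| q | s = 1 | s = 0.5 | s = 0 |
|---|---|---|---|
| 5% | 1.0; 64% | 0.5; 40% | 0 |
| 13.1% | 2.6; 94% | 1.3; 74% | 0 |
| 20% | 4.0; 99% | 2.0; 88% | 0 |

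At q = 13.1% and s = 1: 20 × 0.131 = 2.6, and 1 − 0.869^20 = 0.94.

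The exact 95% interval is 0% to 17% for 0/20 and 3% to 38% for 3/20. These overlap, so the reported result would not by itself show whether a low count came from few added cancers or from few being sampled.

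**The case against.** The best reply is that the two sections can be read together. Both use a scale-of-operation test and both give the unknown false positive rate as the reason. Section 3.1 adds for Cohort 2 that surgeons will not remove significantly more than intended. On that reading, additional surgery in section 6.3 simply means a larger operation. It is possible, but the wording does not say so. Section 6.3 already has its own scale test two sentences earlier, so the later bar would add nothing. Section 3.1 also allows about ten extra minutes for viewing and for removing nodules for study purposes, so it does foresee study-driven removal.

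Other parts of the reply stand and limit the point:

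- A reader might infer that the sections command opposite actions. They do not. Section 3.1 is permissive, and leaving the lesion in place complies with both.
- A reader might infer that section 6.3 makes every biopsy depend on suspicion of cancer. It also leaves biopsy of a residual lesion to the surgeon without that condition.
- A reader might infer from the 52% specificity in section 1.4 that false positives among added lesions will be common here. That figure is not from lung and says nothing about how often added lung lesions occur. The same section places most colorectal false positives in reproductive organs and reports the 21 additional colorectal lesions as malignant. Section 7.2 expects patients with several nodules seldom to reach surgery.
- A reader might infer that lesions left behind are never resolved because the schedule lists no scan, or that waiting for a trusted false positive rate is circular. CT monitoring can be routine care, and section 6.3 does not say that the rate must come from added lesions.

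**Conclusion.** The inconsistency is real but narrow: it covers minor-removal lesions seen by imaging alone. For those, one section permits removal and the other does not, and patients may be handled differently under one protocol.

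Primary sensitivity is not affected. The confirmed-extra-lesion proportion in section 3.2 is exposed through its yield. It counts confirmed cancers only and contains no predictive value, so false positives do not enter it. The all-lesion sensitivity and satellite-nodule predictive values in section 7.1 are exposed through selective verification. A reader might extend the point to the false-positive review in Cohort 1. That follows only if an added lesion counts as a subject's false positive, which the protocol does not say.

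The size is unknown. The 0 to 4 subjects in the illustration depend on an assumed frequency, in part borrowed from colorectal surgery, and on extreme values of s. The direction for predictive value assumes that the surgeon's suspicion is informative. In a 20-subject pilot with mainly descriptive analysis, this is a moderate point on statistical grounds. The resection instructions should be reconciled in any case. Which surgical rule is right is for the investigators.

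**What to change.** 1. Reconcile sections 3.1 and 6.3 into one rule, stated once and cross-referenced from the other section. The choice of rule stays with the investigators. If a temporary restriction is kept, say what ends it.
2. In the electronic report form, record two items for each additional fluorescent lesion: whether it was suspected without fluorescence, and its disposition (removed, biopsied or left). Section 3.1 already requires nodules to be documented, and the first exploratory outcome in section 3.2 already implies the first item.
3. Count lesions left without pathology as unverified and do not drop them. With *v* verified added fluorescent lesions, *t* of them malignant, and *u* unverified, report the positive predictive value with bounds from t/(v + u), all unverified benign, to (t + u)/(v + u), all unverified malignant. The false-positive proportion, taken as the benign share of added fluorescent lesions, is one minus these. Give *u* beside the all-lesion sensitivity.

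The cost is some protocol wording and two form fields, with no added patients or procedures. The predictive value reported for added lesions may look less favourable.

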### 3.2 Study Endpoints

#### Efficacy

Efficacy will be assessed through determination of the sensitivity and specificity of SGM-101 uptake and expression in identifying non-small cell lung cancer. Additional exploratory efficacy outcomes will include:

- Number of lung nodules lesions identified under usual visual/tactile conditions compared with such lesions identified using SGM-101 and fluorescence imaging
- Number of lymph nodes with metastatic cancer that are identified using visual/tactile conditions compared with such lesions identified using SGM-101 and fluorescence imaging
- Proportion of subjects in whom more lesions are identified using SGM-101 with fluorescence imaging and subsequently confirmed by pathology/immunohistochemistry analysis as cancer compared with using usual visual/tactile conditions to identify such lesions
- Number of cases that surgeon cuts through tumor and the positive margin is detected by the imaging of SGM-101.

#### Safety

The safety of the study will be determined via incidence rates of all AEs and treatment-emergent AEs (TEAEs) from the time of SGM-101 administration through follow-up.

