### 5.2 Treatment Regimen

The proposed dose of SGM-101 to be explored in this study is 5-10 mg to be administered intravenously over 30 minutes followed by a 50 mL flush of isotonic saline to account for the dead volume of the tubing. SGM-101 will be administered 3 to 5 days (+/-1 day) prior to surgery..

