#### Adverse Event Reporting Period

The study period during which adverse events must be reported is from the time the subject checks-in for SGM 101 study dye infusion visit until completion of subject's post-operative visit (approximately 2-4 weeks after visit 3 date of surgery). The following common surgical adverse events with a start date occurring after the subject's surgical procedure has begun will not be captured unless the adverse event remains a grade 4 at discharge: pain, Nausea, Vomiting, Fatigue, Inflammation, Swelling, Tenderness at the site of incision, Pneumothorax, Atelectasis, Hemothorax,

Hydropneumothorax, Drain placement for fluid retention and air leak, Excision site pain, Atrial Fibrillation, Renal Insufficiency, Constipation, Anemia, Sinus Bradycardia, Crepitus, Stress, Urinary Retention, Drowsy, Light headedness, Headache, Pneumonia, Hypotension, Hypertension, Frustration, Irritability, Restlessness, and Insomnia.

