#### Abnormal Laboratory Values

A clinical laboratory abnormality should be documented as an adverse event if any one of the following conditions is met:

1. The laboratory abnormality is not otherwise refuted by a repeat test to confirm the abnormality
2. The abnormality suggests a disease and/or organ toxicity
3. The abnormality is of a degree that requires active management; e.g. change of dose, discontinuation of the drug, more frequent follow-up assessments, further diagnostic investigation, etc.
4. The post-surgical laboratory abnormality falls outside the following ranges:
  - a. Glucose: 50-500mg/dl
  - b. Red Blood [contact] MII/uL
  - c. Hemoglobin: 6.75-20.00g/dL
  - d. Hematocrit: 20.0-60.0%
  - e. Creatinine: 0.3-5.0mg/dL
  - f. Sodium Level: 110-180mmol/L
  - g. Potassium Level: 2.5-8.0mmol/L
  - h. Chloride: 80-150 mmol/L
  - i. CO2: 10-60mmol/L
  - j. Calcium Level: 6.0-20.0 mg/dL

5.

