### 8.2 Recording of Adverse Events

At each contact with the subject while on the study, the investigator must seek information on adverse events by specific questioning and, as appropriate, by examination. Information on all adverse events should be recorded immediately in the source document, and also in the appropriate adverse event module of the case report form (CRF). All clearly related signs, symptoms, and abnormal diagnostic procedures results should be recorded in the source document, though should be grouped under one diagnosis.

The clinical course of each adverse event should be followed until resolution, stabilization, or until it has been determined that the study treatment or participation is not the cause. Serious adverse events that are still ongoing at the end of the study period must be followed up to determine the final outcome. Any serious adverse event that occurs after the study period and is considered to be related to the study treatment or study participation should be recorded and reported immediately.

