#### **8.4 Reporting SAE's to the DSMC**

All on-site SAEs for Penn subjects regardless of attribution or expectedness must be submitted to the DSMC within 10 days. Reports will be sent to the DSMC for **90 days** following the last date the subject received study treatment/therapy or was exposed to an investigational device.

All unexpected deaths or deaths related to the study agents/device must be reported within 24 hours. All other deaths should be reported within 30 days.

All adverse events which meet the following criteria will also be managed as described below:

All Grade 3 or higher events will be reported to the DSMC within 10 days of knowledge of the event. All unexpected deaths will be reported within 24 hours of knowledge of the event.

All other deaths will be reported within 30 days of knowledge of the event.

In addition, any adverse events will be recorded promptly in CTMS (clinical research management database).

In addition, any adverse events will be recorded in CTMS (clinical research management database).

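### Section 8.1 drops 31 event types once surgery starts, even if serious, Grade 3 or drug-related, and so contradicts the all-AE safety endpoint and Sections 8.2 and 8.4

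*Protocol*

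**What the plan says.** - **Endpoint.** Section 3.2 (Safety) measures safety by "incidence rates of all AEs and treatment-emergent AEs (TEAEs) from the time of SGM-101 administration through follow-up".
- **AE definition.** Section 8.1 (Adverse Event) covers any symptom, sign or illness that appears or worsens during the study, with no carve-out for surgery.
- **Window.** Section 8.1 (Adverse Event Reporting Period) runs from check-in for the infusion visit "until completion of subject's post-operative visit (approximately 2-4 weeks after visit 3 date of surgery").
- **Exclusion.** The same subsection lists event types that, with onset after surgery has begun, "will not be captured unless the adverse event remains a grade 4 at discharge". The list includes pneumonia, atrial fibrillation, hypotension, hemothorax, renal insufficiency and anemia.
- **Laboratory rule.** Section 8.1 (Abnormal Laboratory Values) counts a result as an AE if, among other conditions, "The post-surgical laboratory abnormality falls outside the following ranges". Those ranges include hemoglobin 6.75 to 20.00 g/dL and creatinine 0.3 to 5.0 mg/dL.
- **Recording.** Section 8.2: "Information on all adverse events should be recorded immediately in the source document", and also in the CRF.
- **Reporting.** Section 8.4 sends every on-site SAE to the DSMC, whatever its cause and whether or not it was expected. It adds "All Grade 3 or higher events will be reported to the DSMC within 10 days of knowledge of the event" and that "any adverse events will be recorded promptly in CTMS".

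**The concern.** The endpoint promises one thing and the capture rule delivers another. If site staff follow the reporting-period list, a listed event after surgery stays out of the safety data however severe it was and whatever caused it, unless it is still grade 4 at discharge. If they follow 8.2 and 8.4, the same event is recorded and, when serious or Grade 3 or higher, also reported. The same 20 subjects could then give different values of the stated safety endpoint, depending on which section was followed.

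This differs from detail that an analysis plan can supply later. An event that was never recorded cannot be recovered at analysis. Two features of the protocol make the related-event gap more than a formality:

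- Section 3.1 names nausea and vomiting among the effects that the added anesthesia time for imaging could make more likely. Both are on the excluded list.
- Section 7.1 monitors adverse reactions with a Bayesian rule. A listed reaction that is not captured may never reach that rule.

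**Working it through.** The plan states no figure on this point, so there is nothing to reproduce. The check is a count, a comparison of rules, and two short calculations for context.

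**1. Count.** Splitting the reporting-period list at its commas, from pain to insomnia, gives 31 event types.

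**2. The rules side by side,** for a listed event that starts after surgery begins:

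| Event | 8.1 reporting period | 8.2 | 8.4 |
|---|---|---|---|
| Grade 1-2, non-serious, unrelated | not captured | recorded | CTMS |
| Grade 1-2, related to SGM-101 | not captured | recorded | CTMS |
| Grade 3 | not captured | recorded | DSMC and CTMS |
| Grade 4, improved before discharge | not captured | recorded | DSMC and CTMS |
| Still grade 4 at discharge | captured | recorded | DSMC and CTMS |
| Serious (on-site), not grade 4 at discharge | not captured | recorded | DSMC and CTMS |
| Fatal before discharge | outside the literal exception | recorded | DSMC and CTMS |
| Starts after discharge | exception cannot be met | recorded | CTMS; DSMC if on-site SAE or Grade 3+ |

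The sections agree in one row of eight. The protocol gives no order of precedence.

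**3. Worked case.** A Grade 3 pneumonia after surgery that prolongs the stay meets the SAE definition in 8.1. It goes to the DSMC under 8.4 on two grounds, seriousness and grade. Under the reporting-period list it is not captured.

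**4. Laboratory overlap.** A post-surgical hemoglobin below 6.75 g/dL, or creatinine above 5.0 mg/dL, is an AE under the laboratory rule. Anemia and renal insufficiency are on the excluded list. The overlap is mainly these two conditions, at extreme values.

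**5. Share of the window with full capture.** Section 5.2 states "SGM-101 will be administered 3 to 5 days (+/-1 day) prior to surgery", so the interval from infusion to surgery is 2 to 6 days. Follow-up after surgery is about 14 to 28 days.
- Largest share: 6 / (6 + 14) = 30%.
- Smallest share: 2 / (2 + 28) = 6.7%.

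These are shares of calendar time, not of events. Unlisted events are still captured after surgery.

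**6. Drug remaining at surgery.** Section 1.2 gives a preliminary mean half-life of about 30 h. Assuming simple exponential decline, the fraction remaining is 2^(-t/30):
- 3 days (72 h): 2^(-2.4) = 19%
- 5 days (120 h): 2^(-4) = 6%
- With the one-day allowance, 2 days (48 h): 2^(-1.6) = 33%; 6 days (144 h): 2^(-4.8) = 4%

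Most exposure precedes surgery, but some can continue into the period of partial capture.

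**The case against.** The strongest reply is that 8.1 holds the definitions, and a specific rule governs a general one. On that reading, all AEs in 3.2 and 8.2 means AEs reportable under 8.1. Leaving out expected surgical events is common and sensible in a single-arm study, where routine post-operative pain or constipation says little about the agent. This stands in part. A reader might infer that the safety endpoint cannot be computed at all. The documents do not support that: a rate of captured AEs can be computed, and it is the label that is wrong. The reply does not rescue the rest, because under it a listed Grade 3 event still breaches 8.4 if it goes unrecorded. If 8.4 prevails instead, the list in 8.1 is wrong as written.

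A second reply is that staff can comply with both: keep listed events out of routine AE data while reporting serious and Grade 3 or higher ones to the DSMC. This largely answers any inference that subjects are left unprotected. It does not bring those events into the endpoint, and 8.4 also wants every AE in CTMS.

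A third is that 8.1 (Hospitalization, Prolonged Hospitalization or Surgery) lets the protocol make exceptions to SAE reporting. That clause concerns hospitalization. It does not reach the Grade 3 rule in 8.4 or the recording rule in 8.2.

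It is also fair that the laboratory ranges are wide for the same reason as the list, so that conflict is narrow. Tabulating AEs before and after the start of surgery is ordinary analysis-plan content, and its absence here is no fault.

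**Conclusion.** The contradiction is real and can be shown from the protocol alone. The exclusion covers 31 event types, has one narrow exception, and leaves out listed events that are serious, fatal, Grade 3 or higher, drug-related or first seen after discharge. It conflicts directly with 8.2 and 8.4, and narrowly with the laboratory rule.

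Its numerical effect is unknown. A reader might infer a particular under-count in the 20 subjects, but the protocol gives no expected frequency for the listed events, so any such figure would be invented. If 8.2 and 8.4 are followed in full, nothing is lost. If the list is followed as written, the loss ranges from trivial Grade 1-2 events to serious or related ones.

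The consequence is modest. This is a descriptive pilot whose primary aim is diagnostic performance, and events between infusion and surgery are fully captured. The change is worth making because it is cheap and unrecorded events cannot be restored later.

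**What to change.** 1. **Section 8.1, Adverse Event Reporting Period.** State that the exclusion never applies to a listed event that is serious or fatal, that reaches Grade 3 or higher at any time, that is judged related to SGM-101 or to study procedures, or that lies outside the post-surgical laboratory ranges in the same section. Define study procedures as the infusion and the imaging with its added anesthesia time, not the standard operation; otherwise every surgical event would qualify. The grade-4-at-discharge clause then becomes redundant and can go.
2. **Sections 3.2 and 8.2, and the CTMS sentence in 8.4 (which appears twice).** Limit the all-AE wording to AEs captured under 8.1. The reported rate is then correctly labelled as excluding unrelated, non-serious Grade 1-2 listed surgical events.
3. **Optional.** The analysis plan may report the fully captured interval from infusion to surgery separately. No protocol change is needed for this, since the exclusion already depends on start dates.

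The cost is wording in four sections and slightly more post-operative recording, with no new visits, procedures or subjects. Unrelated Grade 1-2 listed events after surgery stay uncounted, but the label would now say so.
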